#### 7.1.1 Kenya

The study is part of a multi-year collaboration between LSTM and the Kenya Medical Research Institute (KEMRI), Kisumu, western Kenya, and the US Centers for Diseases Control and Prevention (CDC)-Kenya, and will be conducted in approximately 3 to 5 Hospitals and satellite ANC clinics in the counties of the previous Western and Nyanza Provinces; including, but not limited to Busia, Siaya, Ahero, Homa Bay and Migori counties in high malaria transmission areas in western Kenya.

### 7.1.2 Malawi

The sites in southern Malawi will include 3 to 5 district hospitals and satellite ANC clinics where several pregnancy studies have been conducted. The Research Support Centre from the College of Medicine (CoM), University of Malawi, and supported by Malawi-Liverpool-Wellcome Trust Clinical Research-Programme linked with the CoM in Blantyre will be the coordination institutions providing administrative and laboratory support.

## 7.2 ELIGIBILITY CRITERIA

### 7.2.1 Inclusion criteria

Pregnant women between 16-28 (both inclusive) weeks gestation, who have a viable singleton pregnancy, resident of the study area, willing to adhere to scheduled and unscheduled study visit procedures, and willing to deliver in a study clinic or hospital.

### 7.2.2 Exclusion criteria

Multiple pregnancies (i.e. twin/triplets), HIV-positive, known heart ailment, severe malformations or nonviable pregnancy observed by ultrasound, history of receiving SP during this pregnancy, unable to give consent, known allergy or contraindication to any of the study drugs.

## 7.3 INTERVENTIONS

### 7.3.1 Trial Medications and interventions

#### 7.3.1.1 Name and description of study arms

All women will be randomly allocated to receive one of three IPTp regimens at enrolment and at each subsequent monthly ANC visit during the 2nd and 3rd trimesters. The range will be 3 to 7 visits depending on the gestational age of the woman at enrolment and delivery. Because recruitment is restricted to 16-28 weeks gestation, a median of 4 to 5 courses is expected.

1. **IPTp-SP:** This is the control arm and consists of a standard single-day stat course of 3 tablets of quality-assured SP (tablets of 500 mg of sulphadoxine and 25 mg of pyrimethamine) provided at enrolment and at each subsequent monthly ANC visit in the 2nd and 3rd trimester.
2. **IPTp-DP:** 3 to 5 tablets of DP (tablets of 40 mg of dihydroartemisinin and 320 mg of piperaquine, based on bodyweight) daily for 3 days provided at enrolment and at each subsequent monthly ANC visit in the 2nd and 3rd trimester plus 1gr (as 2 x 500mg equivalent tablet of placebo AZ daily for 2 days at enrolment. The dose of DP is equivalent to the standard treatment (case-management) dose for malaria in adults recommended by WHO with a target dose (range) of 4 (2-10) mg/kg bodyweight per day dihydroartemisinin and 18 (16-27) mg/kg bodyweight per day piperaquine given once a day for 3 days for adults and children weighing  $\geq 25$  kg (36-60 kg: 3 tablets, 60-80 kg: 4 tablets,  $\geq 80$  kg 5 tablets). One 3-day course will be provided at enrolment and again at each subsequent monthly ANC visit in the 2nd and 3rd trimester. The weight at enrolment will be used to define the weight class to guide treatment both at enrolment and subsequent scheduled visits.
3. **IPTp-DPAZ:** 3 to 5 tablets of DP (based on bodyweight) daily for 3 days provided at enrolment and at each subsequent monthly ANC visit in the 2nd and 3rd trimester, plus 2 tablets of AZ (500 mg) daily for 2 days (2 g total over 2 days) at enrolment. The dose of AZ is the standard dose for the treatment of STIs/RTIs.

Table 2: Dosing regimen per course

| Study arm | Drug       | Number of tablets once daily per course |        |        |
|-----------|------------|-----------------------------------------|--------|--------|
|           |            | Day-0                                   | Day-1  | Day-2  |
| IPTp-SP   | SP         | 3                                       | 0      | 0      |
|           | Total      | 3                                       | 0      | 0      |
| IPTp-DP   | DP*        | 3 to 5                                  | 3 to 5 | 3 to 5 |
|           | Placebo-AZ | 2                                       | 2      | 0      |
|           | Total      | 5 to 7                                  | 5 to 5 | 3 to 5 |
| IPTp-DPAZ | DP*        | 3 to 5                                  | 3 to 5 | 3 to 5 |
|           | AZ         | 2                                       | 2      | 0      |
|           | Total      | 5 to 7                                  | 5 to 7 | 3 to 5 |

**SP:** stat course of 3 tablets of quality-assured SP (tablets of 500 mg of sulphadoxine and 25 mg of pyrimethamine); **DP:** 3 to 5 tablets of DP (tablets of 40 mg of dihydroartemisinin and 320 mg of piperaquine, based on bodyweight) daily for 3 days (36-60 kg: 3 tablets, 60-80 kg: 4 tablets,  $\geq 80$  kg 5 tablets). **AZ:** 2g over 2 days as 1g (2 tablets of 500 mg) per day.

### **7.3.1.2 Administration of the study drugs**

#### **7.3.1.2.1 Day-0**

All doses on day-0 will be provided as directly observed therapy. Participants will be given some clean water for swallowing the tablets. Women will then be observed for thirty minutes. If vomiting occurs during this time the full dose will be repeated. If the participant vomits again after the repeat dose she will be provided with unblinded standard IPTp-SP and not be issued the subsequent doses for that course (if any).

#### **7.3.1.2.2 Day-1 and Day-2 (both DP arms)**

Participants will be given the remaining day-1 and day-2 doses to take at home, with instructions to take one set of the pre-packaged tablets on each of the two days. Approximately 10% of women will be visited by a fieldworker on the third day to check whether they have taken the tablets and whether they have had any problems. This visit shall also serve to determine the availability, use the previous night, and integrity of LLITNs on a random basis.

### **7.3.1.3 Manufacturing and supply of study drugs**

#### **7.3.1.3.1 Dihydroartemisinin-piperaquine and matching placebo**

Dihydroartemisinin-piperaquine (Eurartesim®) will be provided for the purpose of this study by Alfasigma (formerly Sigma Tau), Rome, Italy.

#### **7.3.1.3.2 Azithromycin**

Azithromycin and matching placebo tablets will be provided either by Pfizer as Zithromax®, or as generic azithromycin (and placebo) by other GMP manufactures (e.g Idifarma, a contract manufacturer in Spain, or Universal, Nairobi).

#### **7.3.1.3.3 Sulphadoxine-pyrimethamine**

Quality assured SP will be procured from a GMP qualified manufacturer.

### **7.3.1.4 Procedures for drug handling & accountability**

#### **7.3.1.4.1 Preparation and packaging**

Each manufacturer will be responsible for the labelling of the active drug and will arrange shipment for further packaging and labelling. Bodyweight specific blister packs with the study arm specific active drug and placebo combinations will be prepared by Idifarma or an equivalent organisation or the study pharmacist, such that one box or envelope contains all the study drugs for that participant. Each box or envelope will contain smaller envelopes each containing a blister pack for a specific course. The specific study drug blisters will be kept in the box/envelope until dispensing. Packaging used for all treatment arms will be identical, labelled and blinded to the contents. The study drugs will be prepared and shipped in at least two different batches, to avoid any shelf life limitations.

#### **7.3.1.4.2 Product storage**

All study drugs will be stored in a secure area with access limited to Investigator and authorised study site personnel, and under appropriate storage conditions.

#### **7.3.1.4.3 Product accountability**

The site-PI will be responsible for establishing a system for the correct handling of study drug to ensure that:

1. Deliveries of study drug from the sponsor are correctly received by a responsible person (e.g. pharmacist assistant)
2. Accurate records are maintained for the receipt of study drug, for the dispensing of study drug to subjects and for returned drug.
3. Certificates of delivery and return must be signed preferably by the investigator or authorised personnel and copies retained in the investigator file.
4. Study drug is to be handled and stored safely and properly and in agreement with the given storage instructions.
5. The study drug is to be prescribed only by the principal investigator, co-investigators or study site personnel authorised to do so by the principal investigator.
6. Study drug is dispensed only to study subjects in accordance with the protocol.
7. Subjects must return all unused medication and empty containers to the investigator.
8. At the end of the study, delivery records must be reconciled with records of usage and returned stock. Any discrepancies must be accounted for in writing.
9. Once accounted for, any returned and unused study treatment at the site will be returned to the sponsor for destruction or destroyed locally upon agreement with the sponsor. Drug destruction certificates will be issued that refers to the subject study numbers for subject specific medication that was destroyed.

#### 7.3.1.4.4 Pharmacist, pharmacist assistant or dispenser

All efforts will be made for the preparation, packaging and labelling of the blinded study drug to be performed and documented in accordance with Good Manufacturing Practice (GMP).

### 7.3.2 Criteria for discontinuing or modifying allocated interventions for a given trial participant

#### 7.3.2.1 *Symptomatic malaria*

##### 7.3.2.1.1 Febrile women at enrolment visit

Women who are febrile during the enrolment visit will not be excluded. They will follow the standard enrolment and randomization procedures during that initial visit. In addition, a malaria RDT will be taken. Women who have confirmed malaria by RDT will be treated with a 3-day course of artemether-lumefantrine (AL) for clinical malaria as per national guidelines and will not yet be given the study intervention. The next study course will then be provided during the next scheduled monthly visit. This will be recorded on the CRF. Women with negative RDT will be given study drug as per randomization arm.

##### 7.3.2.1.2 Febrile women during scheduled visits

Similarly, women in any group who attend for a scheduled study appointment with fever and malaria confirmed by RDT will be treated with a 3-day course of AL for clinical malaria and will not be given the study intervention at that visit. This will be recorded on the CRF. The next study course will then be provided during the next scheduled monthly visit. This will be recorded on the CRF. Women with negative RDT will be given study drug as per randomization arm.

##### 7.3.2.1.3 Unscheduled visits

Women diagnosed with symptomatic uncomplicated malaria during the course of the study will be treated with AL and their next scheduled monthly ANC visit postponed until at least two weeks have passed. This will be recorded on the CRF.

### 7.3.2.2 *Allergy to study medication or other safety reasons*

Other reasons leading to withdrawal from study interventions include suspected or confirmed allergic reaction to the study drug or for safety reasons as judged by the investigator, study safety monitor or DMEC. See also paragraph 7.3.5 Strategies to improve adherence to study protocol monitoring .

## 7.3.3 Permitted and prohibited concomitant medication and care

### 7.3.3.1 *Routine care and permitted concomitant medication*

All participants will be offered routine antenatal care according to local policy and the principles of 'focused antenatal care'. This includes the provision of insecticide-treated bed nets (ITNs) free of charge. Routine antenatal care also includes blood screening at the first appointment for syphilis, anaemia and HIV, and the provision of appropriate treatment for these conditions. Because HIV is an exclusion criterion, women diagnosed prior to enrolment as HIV-positive will be excluded from the trial and referred to routine care for assessment, and initiation of cotrimoxazole prophylaxis and appropriate anti-retroviral treatment.

Participants will be counselled to avoid concomitant medications not prescribed by the study clinic, specifically antimalarial drugs or drugs that may be associated with QTc prolongation. All concomitant medications taken during the study will be recorded in the appropriate sections of the CRF with indication, dose information, and dates of administration.

All routine medication used for antenatal care is permitted, with the exception listed under the paragraph 7.3.3.2, Prohibited medication, page 30. Permitted medication includes the use of AL (first line) and quinine or amodiaquine-artesunate (second line) for treatment of uncomplicated malaria, or artesunate or quinine for severe malaria as per national guidelines. As part of their antenatal care participants will be given iron and folic acid supplements (folic acid dose 0.4 mg to 0.6 mg / day) and tetanus vaccination if applicable. Helminth infections will be treated presumptively with albendazole 400 mg / kg single dose for hookworm, trichuriasis and ascariasis.

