#### **7.5.1.5 Routine antenatal care and treatment of illness**

Routine antenatal care and treatment of any illness identified at this visit will be provided as described in section 7.3.3.1, Routine care and permitted concomitant medication, page 30. This will include the provision of an ITN if the woman does not already have one, and advice on sleeping under the net for the entire duration of the pregnancy.

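### Protocol section 7.3.3.1 gives the presumptive albendazole dose per kilogram of bodyweight, very probably a unit error; read literally it is 14.4 g at 36 kg and 32 g at 80 kg

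*Protocol*

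**What the plan says.** Section 7.3.3.1 describes the background care that every participant receives. It opens with a general rule: "All participants will be offered routine antenatal care according to local policy". Later in the same section, after iron, folic acid and tetanus vaccination, it gives a specific dose: "Helminth infections will be treated presumptively with albendazole 400 mg / kg single dose for hookworm, trichuriasis and ascariasis".

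Section 7.5.1.5, on the enrolment visit, relies on that section: "Routine antenatal care and treatment of any illness identified at this visit will be provided as described in section 7.3.3.1".

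For comparison, section 7.3.1.1 doses dihydroartemisinin-piperaquine (DP) by weight, with a "target dose (range) of 4 (2-10) mg/kg bodyweight per day dihydroartemisinin and 18 (16-27) mg/kg bodyweight per day piperaquine". It turns this into tablets by weight band ("36-60 kg: 3 tablets, 60-80 kg: 4 tablets", and 5 tablets from 80 kg upwards) and says that the enrolment weight fixes the band for the whole study.

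The albendazole sentence is in the current body text, not in the description of amendments. Albendazole appears nowhere else in the protocol.

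**The concern.** A single presumptive dose of several hundred milligrams per kilogram, with no weight table, tablet count or ceiling, does not look like a dose that anyone meant to give. The likeliest explanation is that a per-kilogram unit was attached by mistake to a fixed dose.

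What is at stake is the safety of pregnant women. The wording is directive, treatment is presumptive and so does not wait for a confirmed infection, and no arm is exempt. Anyone who dosed from this sentence would give tens of grams.

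The statistical design is not at stake. The instruction is the same in all three arms and does not enter the sample size, the type I error or the primary comparison.

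**Working it through.** **Inputs**

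- Dose as written: 400 mg per kg, once (section 7.3.3.1).
- Body weights: 36, 60 and 80 kg, the edges of the DP weight bands in section 7.3.1.1. The top band has no upper limit.
- Study-drug strengths: a DP tablet contains 40 mg dihydroartemisinin and 320 mg piperaquine; azithromycin is 1 g per day (sections 7.3.1.1 and Table 2).

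The protocol states no total albendazole dose, so there is no figure of its own to reproduce.

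**Step 1: literal dose.** Dose in g = 400 mg/kg × weight in kg ÷ 1,000.

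| Weight | Calculation | Literal single dose |
|---|---|---|
| 36 kg | 400 × 36 = 14,400 mg | 14.4 g |
| 60 kg | 400 × 60 = 24,000 mg | 24 g |
| 80 kg | 400 × 80 = 32,000 mg | 32 g |

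Above 80 kg the dose keeps rising, because no cap is stated.

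**Step 2: is weight-based dosing intended?** The two drugs that the protocol doses per kilogram compare as follows.

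| Element | DP (section 7.3.1.1, Table 2) | Albendazole (section 7.3.3.1) |
|---|---|---|
| mg/kg figure | yes | yes |
| Permitted range | yes | none |
| Weight bands | yes | none |
| Tablets per band | yes | none |
| Which weight to use | enrolment weight | not stated |
| Maximum | 5 tablets in the top band | none |

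Where the authors mean a per-kilogram dose, they give staff what is needed to deliver it. The albendazole sentence could not be carried out without further information that the protocol does not supply.

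**Step 3: size of the discrepancy under one reading.** Assumption: the per-kilogram unit is struck out and nothing else changes. The dose is then a flat 400 mg = 0.4 g.

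- 36 kg: 400 ÷ 36 = 11.1 mg/kg; literal ÷ flat = 14.4 ÷ 0.4 = 36.
- 80 kg: 400 ÷ 80 = 5.0 mg/kg; literal ÷ flat = 32 ÷ 0.4 = 80.

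The literal text would exceed that reading by a factor equal to the woman's weight in kilograms.

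**Step 4: plausibility of bulk only.** The heaviest first-day study-drug load, DP plus azithromycin, is 3 × 360 + 1,000 = 2,080 mg at 36 kg and 5 × 360 + 1,000 = 2,800 mg at 80 kg. The literal albendazole dose is 14,400 ÷ 2,080 = 6.9 and 32,000 ÷ 2,800 = 11.4 times those amounts. These are different drugs, so the ratios say nothing about toxicity. They show only that the literal dose is out of proportion to anything else swallowed in the trial.

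**Step 5: reach.** Section 7.5.1.5 ties section 7.3.3.1 to the enrolment visit. The parallel text for monthly visits, section 7.5.2.4, points to section 7.3.2.1 (Symptomatic malaria) instead, and the sentence itself specifies a single dose. The exposure in question is therefore one dose per woman, not a repeated one.

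**The case against.** The strongest reply is that this is a slip of one unit in text about background care. Albendazole is not a study drug: it is absent from Table 2, from the supply sections and from the packed participant boxes of section 7.3.1.4.1. The section puts local policy first, so clinic staff would probably give whatever they normally give, and few people would hand a patient 14 g or more. Concomitant medication must be recorded with its dose, and section 10.4.1 provides a safety monitor in each country. The protocol also contains no albendazole product information, so the harm from the literal dose cannot be sourced within it.

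Much of this stands. Local practice probably prevents a literal overdose, and the number of women who would be dosed from this sentence cannot be estimated. The last point is also correct: that tens of grams would be unsafe is a clinical judgement, not something the protocol documents. The case that the text is wrong rests on its own inconsistency (steps 1 and 2), not on a toxicity threshold.

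The reply does not rescue the wording. The section refers to local policy and then prints its own number, without saying which prevails. CRF recording and safety monitors may catch an error, but they do not correct the instruction that causes it. That no sensible reader would follow the sentence is a further sign that it is wrong.

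A text-extraction fault is unlikely, because the folic acid dose in the preceding sentence is printed in the same style, but it cannot be excluded without the PDF page.

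**Conclusion.** The concern holds. Section 7.3.3.1 contains a dose instruction that is wrong as written, very probably through a misplaced per-kilogram unit. Followed literally, it calls for 14.4 g at 36 kg, 24 g at 60 kg and 32 g at 80 kg, with no ceiling.

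The arithmetic is exact. Two things remain inference: that the unit is the element in error, and the flat 0.4 g reading behind the 36-fold and 80-fold figures. The sponsor has to confirm the intended dose; this review does not state it.

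The error should be fixed. It does not threaten the trial's conclusions, but it is a safety error in a written instruction for pregnant participants in all arms, and the reference to local policy only partly offsets it.

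**What to change.** Check the dose and unit against the national policies that section 7.3.3.1 invokes. Then do one of two things:

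- correct the sentence to the confirmed dose and unit; or
- delete the number and say that presumptive treatment of helminth infection follows national policy.

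The second is safer if policy differs between Kenya, Malawi and Tanzania, and it removes the question of which source prevails. Until the correction is approved, tell sites in writing not to dose albendazole from this sentence.

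The cost is one line of protocol text, handled under the amendment procedure in section 11.2.2, and one site notification. No analysis, sample size or data collection changes.

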### 7.3.3.2 *Prohibited medication*

Prohibited medication includes antimalarial drugs not prescribed within the trial protocol, and other drugs with antimalarial properties including daily cotrimoxazole prophylaxis. It also includes high dose folic acid supplementation (>1.5. mg/day such as the commonly used 5 mg tablets per day) and antiretroviral therapy. Randomised participants who take prohibited medications resulting in the premature cessation of the study intervention, will remain in the trial and will be included in the primary, intention-to-treat analysis, but excluded from the per-protocol analysis.

## 7.3.4 Strategies to improve adherence to study protocol monitoring adherence

### 7.3.4.1 *Adherence to study protocol and medication*

Where feasible, study participants will be reminded about any follow-up visits through mobile phone contact. All information will be recorded on the appropriate sections of the CRF. Subjects judged to be non-compliant may continue in the study but will be counselled on the importance of taking their study medication as prescribed.

### 7.3.4.2 *Strategies for retention*

During screening and consent procedures, women will be asked whether they live in the catchment area, are willing to adhere to the study protocol, and deliver in a study clinic or hospital. Specifically, potential participants will be asked whether they will be willing and able to comply with the

frequent follow-up schedule and whether they need to travel out of the study area for an extended period during the follow-up period. The 'study catchment area' will be defined for each study site before the start of the study. All participants will be reimbursed for transportation costs to and from the clinic.

GPS position and otherwise, detailed directions to participants' homes as well as contact information, including mobile phone information, will be recorded at enrolment. If women do not return for scheduled follow-up visits, the study team will call them and ask them to come to the clinic for evaluation, offering transport reimbursement, or if women do not have access to a mobile phone, study staff may visit their house to help arrange transport to the clinic if the women are willing to come to the clinic, or, alternately, a study staff member may go to their home for clinical evaluation and to assess if they still wish to participate in the study. The women's travel costs will be reimbursed. All information will be recorded on the appropriate sections of the CRF. Subjects judged to be non-compliant may continue in the study but should be counselled on the importance of taking their study medication as prescribed.

